# Pre and post treatment observation

1. Vital signs including SpO2 will be measured prior to start of LDRT and at the end of LDRT, prior to transport back to the unit and upon arrival at the unit.
2. Vital signs and clinical observation will be done hourly for the first 4h following treatment and then as per best practice clinical guidelines.
3. It would be desirable not to introduce new therapeutic intervention for 24 hours after radiotherapy unless medically necessary. However, clinicians taking care of the patients will be at absolute liberty to continue best practice management of all patients, whether on study or not.

# **OBJECTIVES AND ENDPOINTS**

# **Primary Objective**

1. To assess the feasibility and safety of administered LDRT to patients with severe Covid 19 pneumonia
2. To assess the toxicity of a single dose of LDRT administered to patients with severe Covid 19 pneumonia

# **Secondary Objectives**

1. To determine improvement in Oxygen requirement within 3 days following LDRT
2. To determine ability to come off mechanical ventilation within 7 days following LDRT
3. To determine time to discharge following LDRT
4. To determine time to death by following LDRT

# **Primary Endpoint**

1. Safety/Feasibility – % patients able to complete LDRT without treatment related SAE at 24h following LDRT
2. Toxicity – % patients without worsening of vital signs to assess clinical and respiratory status at 24h following LDRT (CTCAE acute toxicity criteria)

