# **Data Safety Monitoring Committee (DSMC)**

A Data Safety Monitoring Committee (DSMC) composed of 3 individuals (clinician, clinical investigator, statistician) not involved in the study will be constituted that will review the outcome of each of the first 5 patients in each cohort at 24h following treatment. If >1 of the initial 5 patients experience an SAE felt to be related to LDRT by the investigator and/or DSMC, the study will be halted. If ≤ 1 patients experience a related SAE, a total of 10 patients in each cohort will be enrolled. Any SAE observed in any of the additional patients will be reported to the DSMC for review and discussion.

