# **STUDY POPULATION**

# **Inclusion criteria**

1. Be age ≥18 years
2. Have had a positive rtPCR test confirming the diagnosis of COVID-19 from nasopharyngeal swab, Sputum or lower respiratory tract sample
3. Have had clinical signs of severe acute respiratory syndrome or pneumonia (dyspnea, cough, with need for oxygen support at the time of enrolment)
4. Documented SpO2 < 94% while on ambient air during the screening window, and requires supplemental oxygen to maintain SpO2 ≥ 94% during the screening window.
5. Cohort 1: currently not on mechanical ventilation but would need mechanical ventilation if condition worsens (pre-Vent)
6. Cohort 2: currently on mechanical ventilation for ≤ 5 days (on-Vent)
7. Have visible consolidations/ground glass opacities on chest x-ray or computed tomography consisted with Covid 19 pneumonia.
8. The patient, according to the treating physician, has received medical treatment considered best practice as per the institution’s guidelines*, and does not show improvement of Covid pneumonia (i.e., inability to improve oxygenation despite current treatment, need to increase oxygenation and ventilatory support, and/or declining clinical status at current management)
9. Willingness and ability of the subject to comply with scheduled visits, protocol-specified laboratory tests, other study procedures, and study restrictions.
10. Evidence of a signed informed consent/assent indicating that the subject is aware of the infectious nature of the disease and has been informed of the procedures to be followed, potential risks and discomforts, potential benefits, and other pertinent aspects of study participation.

*institutional covid 19 treatment guidelines provided as Attachment

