# **SAMPLE SIZE**

This is a pilot Phase 1b/2, proof of principle, study to determine safety and feasibility of a single dose LDRT for the treatment of severe Covid 19 pneumonia patients who have nearly exhausted conventional available options. Sample size is based on having sufficient patients to reasonably provide descriptive data for feasibility, toxicity and indication of efficacy:

- Cohort 1 (pre-Vent): 5 patients will be treated. If acute treatment related SAE is observed in ≤ 1 of 5 patients at 24h following LDRT, then 5 additional patients will be treated.
- Cohort 2 (on-Vent): 5 patients will be treated. If acute treatment related SAE is observed in ≤ 1 of 5 patients at 24h following LDRT, then 5 additional patients will be treated.

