# **STATISTICAL ANALYSIS**

Descriptive statistics will be used to determine proportion of patients experiencing toxicity, improvement/worsening of oxygenation status, weaning off oxygenation or ventilation, discharge or death on/before 14d and on/before 28d. All endpoints will be summarized descriptively, using mean, median, interquartile range, minimum/maximum, and standard deviation for continuous endpoints, and frequency and percentage for categorical endpoints. The data from the 2 cohorts will be analysed independently.

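### Primary endpoint 2 is called toxicity of LDRT but counts vital-sign worsening from any cause, so disease progression enters the toxicity figure

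*Protocol*

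**What the plan says.** Section 5.1.1 sets two primary objectives. The second is "To assess the toxicity of a single dose of LDRT administered to patients with severe Covid 19 pneumonia". Section 5.1.3 gives one endpoint for each objective:

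- Endpoint 1: "Safety/Feasibility – % patients able to complete LDRT without treatment related SAE at 24h following LDRT". An event counts only if it is related to treatment.
- Endpoint 2: "Toxicity – % patients without worsening of vital signs to assess clinical and respiratory status at 24h following LDRT (CTCAE acute toxicity criteria"). Nothing here ties the worsening to treatment.

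Section 6.1.1 describes a single-arm study with two cohorts. Inclusion criterion 8 (section 8.1.1) admits patients who have not improved on institutional best practice. Among its examples are "need to increase oxygenation and ventilatory support, and/or declining clinical status at current management". Section 16 is descriptive and keeps the cohorts apart: "Descriptive statistics will be used to determine proportion of patients experiencing toxicity", followed by oxygenation change, weaning, discharge and death.

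The decision rules use related SAEs only. Section 15 states, for each cohort: "If acute treatment related SAE is observed in ≤ 1 of 5 patients at 24h following LDRT, then 5 additional patients will be treated". Under section 6.1.2, if more than one of the first five patients "experience an SAE felt to be related to LDRT by the investigator and/or DSMC, the study will be halted". The synopsis, section 6.1.1 and section 17.9 rest on the same event.

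**The concern.** The objective asks a causal question: what harm does a single dose of LDRT do? Endpoint 2 answers a different one: how many patients are worse after 24 hours? The two agree only if almost nobody in this population would worsen without LDRT. The entry criterion makes that an unsafe assumption, and with no control arm the background cannot be subtracted.

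What is at stake is the meaning of a primary result. If the endpoint is reported under its own name, patients whose pneumonia progressed are presented as patients harmed by radiation. That biases the estimate of the stated objective towards more toxicity.

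**Working it through.** **Plan's own figure.** Maximum enrolment is 2 cohorts × (5 + 5) = 20, which matches the synopsis. The sample size is justified descriptively, so there is no power statement to reproduce.

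**What each endpoint measures.** Let q be the 24-hour worsening rate without any LDRT effect, and d the change in that rate caused by LDRT. The objective concerns d. The proportion who worsen estimates q + d, and endpoint 2 as worded is its complement, 1 − (q + d). For an inert dose d = 0, so the proportion who worsen is q. Endpoint 1 would be 100%, provided that every patient completes LDRT and no unrelated SAE is wrongly attributed to it.

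**Size.** The documents give no value for q, so the values below are assumptions. With n = 10 per cohort:

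P(at least 1) = 1 − (1 − q)^10

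P(at least 3) = 1 − [(1 − q)^10 + 10q(1 − q)^9 + 45q²(1 − q)^8]

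| Assumed q | Expected to worsen, of 10 | P(at least 1) | P(at least 3) |
|---|---|---|---|
| 10% | 1 | 0.65 | 0.07 |
| 20% | 2 | 0.89 | 0.32 |
| 30% | 3 | 0.97 | 0.62 |
| 50% | 5 | >0.99 | 0.95 |

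For example, at q = 50% the last column is 1 − (1 + 10 + 45)/1024 = 1 − 56/1024 = 0.945. The mark of 3 in 10 is only for illustration; the protocol sets no threshold.

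**Does the CTCAE reference supply attribution?** No. The adverse event log in the Case Report Form appendix has one column for the CTCAE grade and separate columns for attribution. A grade describes severity, not cause.

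**Related wording.** Section 5.1.3 ties endpoint 2 to CTCAE. Section 7 assigns the grading of acute and late toxicities to the RTOG scale and allows CTCAE for events not related to radiation. The synopsis version of endpoint 2 names vital signs at 24 hours but leaves out the criterion that they have not worsened. These places do not agree on what is counted or how it is graded.

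**The case against.** The strongest reply is that nothing in the trial's conduct depends on endpoint 2. Halting, expansion and the opening of the second cohort all rest on treatment-related SAEs, and vital-sign worsening has no role in any of them. That stands.

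Second, attribution is already collected. Section 7 requires all adverse events to be assessed for relation to treatment and counts exacerbation of existing disease as an adverse event. The log carries graded relatedness codes, and SAE causality is agreed between the principal investigator and the DSMC. This also stands. It makes the repair cheap, but it does not change what endpoint 2 counts.

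Third, section 16 does not define toxicity as vital-sign worsening, and it lists oxygenation change as a separate item. That is right, so the point rests on the label and wording in section 5.1.3. Section 16 matters only because it uses the word toxicity without saying which count is meant.

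Fourth, an all-cause count protects against under-attribution in an uncontrolled study. That is a good reason to keep it, but not a reason to call it toxicity.

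A reader might go further and infer that the protocol leaves open which endpoint decides safety, or that an inert dose would be declared toxic. The documents do not support either reading. Endpoint 1 is labelled as safety and feasibility, and its SAE component alone drives the decisions. Endpoint 2 has no cut-off at which a dose would be declared toxic. In a purely descriptive study with one endpoint per objective, ranking the two or demoting one is a preference, not a correction.

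**Conclusion.** The point holds as a fault in the label and content of one primary endpoint. Endpoint 2 is presented as the toxicity of LDRT but measures all-cause worsening, in a single-arm trial of patients selected because they are failing to improve. Under no treatment effect, its worsening proportion equals the background rate. Across an assumed background of 20% to 50%, the chance that at least 3 of 10 patients in a cohort worsen runs from 0.32 to 0.95; at 10% it is 0.07. These figures rest on assumed rates and on independence between patients. The direction of the bias needs only that some patients worsen from disease.

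Sample size, stopping, expansion and endpoint 1, including its completion component, are unaffected.

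**What to change.** In the synopsis, section 5.1.3 and section 16:

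1. Label endpoint 2 *all-cause clinical worsening at 24h*. Report two counts per cohort: all patients who worsened, and those whose worsening was attributed to LDRT.
2. Base the attributed count on the relatedness codes already on the adverse event log, and state in advance which codes count (for example definite, probable or possible). The log has separate study and drug attribution columns, so name the one to be used.
3. Use the word toxicity only for the attributed count.
4. Reconcile the grading scale between sections 5.1.3 and 7, and bring the synopsis wording of endpoint 2 into line with section 5.1.3.

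Endpoint 1 stays as written, and endpoint 2 need not be ranked below it. The cost is protocol wording, an instruction to enter each 24-hour worsening on the adverse event log, and one extra table row. The downside is that attribution is a judgement in an uncontrolled study, which is why the all-cause count must stay beside it.

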# **PROTOCOL SUMMARY**

# **SYNOPSIS**

| Study description: | Hypothesis: Low-dose radiation therapy (LDRT) improves clinical, radiographic, and immune outcomes in hospitalized patients with covid-19 pneumonia and severe acute respiratory syndrome.  This study investigates LDRT as a selectively localized anti-inflammatory treatment to induce focal suppression of pulmonary immuno-toxicity within viral pneumonia infiltrates in hospitalized patients with COVID19.  Study: Administration of low dose whole lung radiotherapy (LDRT) for the treatment of severe COVID 19 pneumonia in patients on or requiring mechanical ventilation |
| --- | --- |
| Objectives: | To investigate safety and feasibility (primary endpoint) of low dose whole-lung radiation therapy (LDRT) in critically-ill patients with COVID-19 pneumonia, and to explore secondary efficacy endpoints: (1) clinical, (2) respiratory, and (3) outcome  **Primary Objective:**   1. To assess the feasibility and safety of administering LDRT to patients with severe Covid 19 pneumonia 2. To assess the toxicity of a single dose of LDRT administered to patients with severe Covid 19 pneumonia   **Secondary Objective:**   1. To assess improvement in oxygen requirement within 3 days following LDRT 2. To determine ability to come off mechanical (or avoid mechanical) ventilation within 7 days following LDRT 3. To determine time to discharge following LDRT 4. To determine time to death following LDRT |
| Endpoints | Primary   1. Safety/Feasibility – ability to complete LDRT without treatment related SAE 2. Toxicity – vital signs to assess clinical and respiratory status at 24h following LDRT   Secondary   1. Efficacy - ability to be weaned off pre-LDRT ventilatory or oxygen support at 3d post LDRT (% of patients) 2. Efficacy – ability to come off (or avoid) ventilatory support at 7d post LDRT (% of patients) 3. Efficacy - discharge or death by 14d / 28d post LDRT (% of patients) |
| SAMPLE SIZE | Up to 20 participants will be enrolled on this study.   - Cohort 1 (pre-Vent): Up to 10 participants - Cohort 2 (on-Vent): Up to 10 participants |
| Study population | 1. Patient with rtPCR and Xray/CT proven Covid 19 pneumonia who have not responded to conventional therapy and:   Cohort 1: would need mechanical ventilation if condition worsens (pre-Vent)  Cohort 2: has been on mechanical ventilation, but for not more than 5 days (on-Vent) |
| Phase: | Pilot Phase 1b/2 study |

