# Treatment logistics in compliance with hospital infection control guidelines

1. COVID patients for trial to be treated after normal working hours
2. One Linac room will be dedicated for the treatment of all protocol patients (same on each treatment day)
3. Pre and post use cleaning and decontamination of RT suit as per hospital infection control protocol
4. Use of UVC light in the RT room after completion of treatments to further reduce risk of infection
5. All personnel and staff involved in the treatment/transportation/transfer of the patient will be in full PPE and will donn and doff per hospital infection control guidelines. All accessories and other mobile items to be removed from the Linac room
6. All surfaces to be covered by disposable plastic sheets – Linac couch, head of Linac, hand pendant, accessories used
7. Items for re-sterilization and re-use to be put in specially marked bag and left inside the Linac room
8. The Linac room is equipped with negative pressure for purposes of general radiotherapy with a 100% fresh air exchange.

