# **STUDY DESIGN**

# **Overall design**

This is a pilot Phase 1b/2 study to determine safety and feasibility of administering LDRT to the whole lung in a Covid 19 patient population who have progressed following administration of conventional therapy and are on ventilatory support or who are decompensating despite conventional therapy and are at risk of requiring ventilatory support to sustain life.

The rational basis is the effort to influence the pulmonary immune repertoire that is responsible for the cytokine storm responsible for the ARDS that leads to the need for mechanical ventilatory support in such patients. Previous experience at Emory University has been very favourable ^17^ Of the 10 patients (median age 78) who were requiring supplemental oxygen whose health was visibly deteriorating, received a single dose of 150 cGy. Patients were in and out of the RT unit within 10-15 minutes. Within 24h, 9/10 patients showed rapid improvement and were discharged within 12 days. No acute toxicity was observed (personal communication ahead of publication). In the meantime, there are 5 active trials studying the ability of various strategies of LDRT in Covid 19 patient population.

Our study determines to assess the safety and feasibility of administering LDRT in the LMIC setting in patients who may have different comorbidities than seen in the West, where extraordinarily expensive therapeutic agents may not be available, and where ventilators are in extremely short supply.

A single dose of LDRT is seen as a relatively inexpensive treatment in patients at the extreme end of the clinical spectrum of Covid 19 pneumonia (on ventilators or destined to need ventilator support).

Eligible patients will receive a single dose of LDRT of 100cGy which has been found to be safe and efficient is comparable settings. Patients will be followed for toxicity for the duration of their hospital stay with specific study related endpoints being determined at 24h, 3d, 7d, 14d, and 28d.

This will be a single arm, single dose pilot study involving 2 separate cohorts (Cohort 1: pre-Vent / Cohort 2: on-Vent). 5 patients will be initially enrolled on each cohort. If ≤ 1 patients experience an acute LDRT associated SAE, an additional 5 patients for a total of 10 will be enrolled.

Special labs will be collected from participants for future testing as biological correlates of response of progression.

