**POST-DOSE (Day 1)**

| **Time-point** | **Actual Time** | **BP** | **TEMP** | **Pulse** | **RR** | **SPO2** | **O2 (L)** | **Comments (AEs, etc.)** |
| --- | --- | --- | --- | --- | --- | --- | --- | --- |
|  |  | mmhg | C | b/min | b/min | % |  |  |

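### The primary toxicity endpoint is worded as vital-sign status at 24 hours: read literally, it omits worsening that resolves sooner, leaves the scoring of an early death open, and has no timed 24-hour reading behind it

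*Protocol*

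**What the plan says.** The Primary Endpoint section lists two endpoints. The first is the percentage of "patients able to complete LDRT without treatment related SAE at 24h following LDRT". The second, for toxicity, is the percentage of "patients without worsening of vital signs to assess clinical and respiratory status at 24h following LDRT", with a reference in brackets to CTCAE criteria for acute toxicity. The Synopsis gives the second as "Toxicity – vital signs to assess clinical and respiratory status at 24h following LDRT", with neither a notion of worsening nor a time window. The Overall design section speaks of "specific study related endpoints being determined at 24h, 3d, 7d, 14d, and 28d".

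Monitoring is densest early. The section on pre and post treatment observation, repeated under Safety Monitoring, asks for vital signs before LDRT, at its end, before return to the unit and on arrival. Then "Vital signs and clinical observation will be done hourly for the first 4h following treatment", after which frequency follows usual care. The case report form has a pre-dose chart and one headed "POST-DOSE (Day 1"); as shown, neither has a printed 24h line. The next scheduled set is on Day 2 (schedule of events; study procedures for Days 2 and 4-6), with no clock time or window. The treatment logistics section adds "COVID patients for trial to be treated after normal working hours".

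**The concern.** This is one of two primary endpoints, and the only one that does not depend on a judgement of relatedness to LDRT. If it means status at 24h and nothing else, a patient who desaturates two hours after irradiation and transfer, and is back at baseline the next day, counts as free of toxicity. A patient who dies at hour 12 has no 24h vital signs. If that death is judged unrelated, it does not count against the first endpoint either, and the protocol does not say whether the second treats it as worsening, missing or excluded.

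The early readings cover the exposure that this trial adds to usual care, namely transfer and irradiation. No section gives them a role in the endpoint. The endpoint's time frame and the visit schedule are fixed in the protocol, and an analysis plan cannot supply a timed reading that was never scheduled.

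**Working it through.** **1. Figures in the plan.** The sample size is descriptive and there is no power calculation to reproduce. The one check is 2 cohorts × (5 + 5) = 20, which agrees with the stated maximum of 20.

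**2. Is the 24h wording a landmark or a period?** The protocol is not consistent across its own rules:

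| Item | *At* a time | Period wording |
|---|---|---|
| Related SAE, 24h | Sample Size | DSMC section under Ethics (within) |
| Ventilation, 7 days | Synopsis | Secondary Endpoint (within) |
| Discharge or death, 14/28 days | Secondary Endpoint | Statistical Analysis (on or before) |
| Vital-sign toxicity, 24h | Synopsis, Primary Endpoint | none |

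The first three items appear both ways. The toxicity endpoint appears only as *at*. The Statistical Analysis section promises a proportion experiencing toxicity but names no window.

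**3. Post-dose readings specified by hour 4.** End of LDRT, before transport and arrival make 3, or 2 if the first two are one reading. Adding 4 hourly sets gives 7, or 6.

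**4. Direction.** Anyone worse at 24h is also worse at some time through 24h. The percentage without worsening is therefore never lower under the landmark reading than under the cumulative one. Dropping early deaths does not reverse this: with a successes among n treated and d early deaths, a/(n − d) ≥ a/n.

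**5. Size.** Let k be the number of patients in a cohort of 10 with an early event (worsening resolved by 24h, or death before 24h) and no other worsening. The values of k are assumptions. Intervals are exact (Clopper-Pearson) 95%.

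| k | Any worsening or death through 24h | Status at 24h, all k transient | All k deaths, dropped |
|---|---|---|---|
| 1 | 9/10 = 90% (55.5-99.7) | 10/10 = 100% (69.2-100) | 9/9 = 100% (66.4-100) |
| 2 | 8/10 = 80% (44.4-97.5) | 10/10 = 100% (69.2-100) | 8/8 = 100% (63.1-100) |
| 3 | 7/10 = 70% (34.8-93.3) | 10/10 = 100% (69.2-100) | 7/7 = 100% (59.0-100) |

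Each event is worth 1/10 = 10 points, or 1/5 = 20 points in a cohort that stops at 5.

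**6. How likely is at least one early event in 10?** The documents give no 24h risk, so p is assumed. The chance is 1 − (1 − p)^10: 40% for p = 5%, 65% for 10%, 89% for 20% and 97% for 30%.

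**The case against.** The strongest reply is that the defect is ambiguity and not an established single-time-point design. Given the loose use of *at* and *within*, and the reference to CTCAE acute toxicity criteria, the endpoint can be read as toxicity up to 24h. That stands. A reader might infer that one reading decides the endpoint and that the earlier ones are discarded, but no section says either.

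A reader might also infer that a death before 24h is not registered. The documents do not support that. They are silent on its scoring in this endpoint, and such detail can reasonably sit in an analysis plan. A fatal event is an SAE, the DSMC is alerted to any SAE and meets within 24 hours, and it reviews each of the first five patients per cohort at 24h. All adverse events are documented, and the log records start time and CTCAE grade, so the transient event in the example would be recorded. What is uncertain is only whether it counts in the primary endpoint.

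Finally, because treatment is given after hours, a reader might infer that the 24h value is really a next-morning value. If LDRT is at 18:00-21:00 and the round at 07:00-09:00, the interval would be 10 to 15 hours (21:00 to 07:00; 18:00 to 09:00). Those clock times are assumptions, and no section ties the endpoint to a morning round. The daily form records the time of assessment, and the ICU and HDU monitor around the clock, so readings near 24h should exist. What survives is that the protocol does not fix one.

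**Conclusion.** The point holds as a defect of definition in a primary safety endpoint. The literal wording counts only worsening present at 24h and leaves early death open, and no timed 24h reading is scheduled. A cumulative reading is possible, and the two can differ by 10 points per early event in a full cohort. The direction is certain: the literal reading cannot give the less favourable figure. The size depends on event counts that are assumed here.

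The consequence is bounded. No figure in the protocol is wrong and the analysis is descriptive. The rule for expanding or halting a cohort uses related SAEs, so it is unaffected. Safety oversight does not depend on this endpoint. The change is still worth making, because the reported toxicity percentage is a main result of the trial and should not turn on an unstated reading.

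**What to change.** In both the Primary Endpoint section and the Synopsis, define the endpoint as the percentage of all treated patients with no worsening at any time from the end of LDRT through 24h.

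- **Threshold:** an increase in CTCAE grade relative to the Day 1 pre-dose reading, so that trivial fluctuations do not count. The endpoint already cites CTCAE and the adverse event log uses version 5. The Adverse Events section names the RTOG scale for acute toxicity, so that section should be reconciled with the endpoint.
- **Death:** death from any cause before 24h counts as worsening, and the patient stays in the denominator.
- **Timing:** add one timed 24h line, with a stated window, to the post-dose chart.
- **Reporting:** give status at 24h as a supportive result.

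The cost is a wording change in two places and one line on an existing chart, using observations that inpatients largely have already. The toxicity percentage may be somewhat less favourable, because transient changes in unstable patients will count. The sample size and the SAE rule of at most 1 in 5 stay as they are.
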